# A phase III multisite randomised controlled trial to compare the efficacy of cannabidiol to placebo in the treatment of cannabis use disorder: the CBD-CUD study protocol

**DOI:** 10.1186/s12888-024-05616-3

**Published:** 2024-03-04

**Keywords:** Cannabis, Cannabis withdrawal, Cannabis use disorder, Cannabidiol, Marijuana, Study protocol

## Abstract

**Background:**

Cannabis use disorder (CUD) is increasingly common and contributes to a range of health and social problems. Cannabidiol (CBD) is a non-intoxicating cannabinoid recognised for its anticonvulsant, anxiolytic and antipsychotic effects with no habit-forming qualities. Results from a Phase IIa randomised clinical trial suggest that treatment with CBD for four weeks reduced non-prescribed cannabis use in people with CUD. This study examines the efficacy, safety and quality of life of longer-term CBD treatment for patients with moderate-to-severe CUD.

**Methods/Design:**

A phase III multi-site, randomised, double-blinded, placebo controlled parallel design of a 12-week course of CBD to placebo, with follow-up at 24 weeks after enrolment.

Two hundred and fifty adults with moderate-to-severe CUD (target 20% Aboriginal), with no significant medical, psychiatric or other substance use disorders from seven drug and alcohol clinics across NSW and VIC, Australia will be enrolled.

Participants will be administered a daily dose of either 4 mL (100 mg/mL) of CBD or a placebo dispensed every 3-weeks. All participants will receive four-sessions of Cognitive Behavioural Therapy (CBT) based counselling. Primary endpoints are self-reported cannabis use days and analysis of cannabis metabolites in urine. Secondary endpoints include severity of CUD, withdrawal severity, cravings, quantity of use, motivation to stop and abstinence, medication safety, quality of life, physical/mental health, cognitive functioning, and patient treatment satisfaction. Qualitative research interviews will be conducted with Aboriginal participants to explore their perspectives on treatment.

**Discussion:**

Current psychosocial and behavioural treatments for CUD indicate that over 80% of patients relapse within 1–6 months of treatment. Pharmacological treatments are highly effective with other substance use disorders but there are no approved pharmacological treatments for CUD. CBD is a promising candidate for CUD treatment due to its potential efficacy for this indication and excellent safety profile. The anxiolytic, antipsychotic and neuroprotective effects of CBD may have added benefits by reducing many of the mental health and cognitive impairments reported in people with regular cannabis use.

**Trial registration:**

Australian and New Zealand Clinical Trial Registry: ACTRN12623000526673 (Registered 19 May 2023).

## Introduction

### Cannabis use disorder

Cannabis is the third most widely used drug in the world, after tobacco and alcohol, with an estimated 209 million persons, or 4.1% of the global adult population having used cannabis in the previous year (2020), Cannabis use has increased by 23 per cent between 2010 and 2020 [1]. Worryingly, between 9 and 22% of people who use cannabis will develop moderate or severe cannabis use disorder (CUD) [2] signifying ongoing cannabis use despite clinically significant impairment in health and social function [2]. The most recent global estimate suggests approximately 22.1 million persons met diagnostic criteria for CUD in 2016 (289.7 cases per 100,000 people) [3, 4].

CUD is associated with an increased risk of numerous psychosocial outcomes, including: (i) mental health problems (e.g., anxiety, depression, psychosis, suicide); (ii) physical illness (e.g. respiratory, cardiovascular disease, cancer); (iii) cognitive impairment (e.g., verbal learning, memory and attention); (iv) impaired brain development with prenatal or adolescent exposure; (v) social harms (e.g. crime, employment, parenting, financial impacts); and (vi) motor vehicle accidents [5].

### Treatment for CUD

Existing treatments for CUD have modest outcomes. Reviews of psychosocial interventions (e.g. cognitive behavioural therapy (CBT), motivational enhancement therapy) [6] and acute withdrawal management [7] indicate that over 80% of patients relapse within 1–6 months of attempting treatment [8–11]. In substance use disorders other than CUD, treatment outcomes are generally optimised when combining medications with psychosocial interventions [12]. Despite examining a wide variety of medications, there are no registered pharmacotherapies for treating CUD [13–15].

There is increasing interest in the use of cannabinoid medications to treat CUD. Promising results have emerged in RCTs with delta-9-tetrahydrocannabinol (THC)-based medications (e.g., nabiximols [16], a 1:1 ratio of THC and CBD) and synthetic THC-based medications (e.g., dronabinol, nabilone) [16, 17]. However, many individuals may not be attracted to cannabinoid ‘agonist’ therapy with THC-based medications as they may have intoxicating, psychotogenic, anxiogenic and addictive properties. Thus, there is growing interest in the potential of non-intoxicating cannabinoids, such as CBD, in the treatment of CUD.

### Cannabidiol and CUD

Cannabidiol (CBD) is one of the many cannabinoids found in the *Cannabis sativa* plant. It has diverse and multiple molecular targets [18] and anti-inflammatory, anxiolytic, anticonvulsant and antipsychotic properties [18–24]. Importantly in the context of CUD, CBD is a negative allosteric modulator of the activity of cannabinoid type 1 receptors within the central nervous system, restricting the ability of THC to bind to these receptors, thus reducing THC action [25]. CBD does not cause intoxication, dependence, or withdrawal on discontinuation, and does not result in positive results in urine or saliva tests used to detect cannabis use [26, 27]. Meta-analyses of clinical trials indicate CBD has a good safety profile [28], including in cannabis-using populations [29], and low oral bioavailability (approximately 6%) with a half-life of 18–32 h that permits once daily dosing [30].

CBD has shown promise in animal studies modelling addiction to a range of other substances, with reductions in self-administration of alcohol, opioids, cocaine, and methamphetamine [31]. Endocannabinoids are important regulators of the brain pathways that mediate neurodevelopment, drug-reward and addiction[32, 33]. In human studies examining other addictive drugs, CBD has been found to significantly reduce cue-induced craving and anxiety during abstinence from heroin [34] and cigarette use among tobacco smokers [35], but was not effective in reducing relapse or cravings in a placebo-controlled randomised trial for cocaine dependence [36].

There has been considerable scientific discussion in recent years about the promise of CBD as a treatment for CUD [37, 38], summarised in a recent review: “According to the previous evidence, it seems that CBD could play a crucial role in the management of CUD [38]”. Preclinical studies suggest that CBD administered to cannabis-dependent rodents reduces the severity of spontaneous withdrawal from THC [39–41]. Despite this, there has been little rigorous clinical research to date examining CBD as a treatment for CUD in humans. Early open-label case studies involving 10 participants with severe CUD indicate that CBD may ameliorate cannabis withdrawal severity and improve anxiety and sleep [39, 42, 43]. These studies used doses varying from 18 to 1200 mg daily but had methodological limitations that limit conclusions regarding efficacy.

A recent Phase 2a adaptive Bayesian RCT [44] demonstrated the promise of CBD for moderate-to-severe CUD and determined suitable doses for further investigations. 82 outpatients diagnosed with moderate-to-severe CUD were randomised to four-weeks of oral placebo (*n* = 23), 200 mg CBD (*n* = 12), 400 mg CBD (*n* = 24), or 800 mg CBD (*n* = 23), each receiving six sessions of motivational interviewing The 200 mg dose arm was eliminated as it was not efficacious following interim analyses. Both 400 mg and 800 mg groups were more efficacious than placebo in reducing cannabis use indicated by self-reported cannabis-free days and urinary carboxy-THC (THC-COOH), the inactive metabolite of THC excreted in urine. Doses were well tolerated with no serious adverse events. Reductions in cannabis use persisted 20-weeks after the four-week intervention in the 400 mg, but not the 800 mg group suggesting that further exploration of the 400 mg dose is warranted. However, the study was not powered to demonstrate efficacy, so larger RCTs are also necessary. The relatively high rates of relapse to heavy cannabis use at follow-up may be attributed to the brief treatment duration (4-weeks) examined in the phase 2a RCT. Indeed, in our previous 12-week RCT of nabiximols, we demonstrated that the full extent of reductions in cannabis use were not achieved until at least week 8 [16]. This suggests a prolonged duration, such as, 12-weeks of CBD and counselling may achieve better outcomes.

In their recent 12-week exploratory, observational, non-randomised, open-label study, Cleirec and colleagues [45] investigated the therapeutic potential of inhaled CBD amongst 20 patients, administered through an electronic vaping device, for the treatment of moderate-to-severe CUD. The average daily dose of inhaled CBD was 216 mg (equivalent to approximately 600–700 mg oral CBD). With a flexible dosing regimen and no formal counselling, the study demonstrated promising outcomes, including a notable 30% (*n* = 6) of participants achieving a 50% reduction in days of cannabis use, and 15% (*n* = 3) reporting complete abstinence by the end of the intervention. The absence of significant adverse events or the need for rescue medications further supports rigorous clinical trials examining the efficacy of CBD for CUD.

Fortin and colleagues [46] recently reported findings from an online anonymous survey of French residents who reported having used CBD within the past month. Respondents reported using CBD primarily to reduce their use of (illicit) cannabis. Of these, 59% (61/105) reported that their CBD use led to a large reduction in illegal cannabis consumption, 35% a moderate reduction, 6% no reduction, and 1% a moderate increase. While the study is limited by the self-report nature of the data and the inherent sampling biases of online surveys, the study provides a consumer perspective of the promise of CBD for treating CUD, complementing findings from the aforementioned preclinical and clinical studies.

In addition to CBD’s potential to facilitate a reduction in cannabis use, prolonged high-dose CBD usage in individuals with CUD may offer an additional advantage—potentially mitigating the adverse cognitive and mental health effects of long-term THC exposure [40, 41]. Animal studies indicate CBD reverses THC-induced memory deficits, conditioned place aversion and decreased social interaction [26]. In a human laboratory study, pre-treatment with CBD reduced acute THC-induced persecutory symptoms and hippocampal-dependent memory impairment [40]. In an open-label study, 10-weeks of daily oral CBD (200 mg) was associated with reduced cognitive deficits, psychotic-like and depressive symptoms and increased hippocampal volumes in chronic cannabis users (daily or near-daily use) (despite continued cannabis use), with the greatest benefits seen in those with cannabis dependence [47]. In the same trial, hippocampal and amygdala functional connectivity with other cortical regions (precentral and lingual gyrus, respectively), changed from pre-to-post intervention, with strong effect sizes (*d* > 1) [48]. However, in a Phase 2a RCT, CBD was not found to significantly impact cognition relative to placebo, except in the 800 mg group [49], although the study was underpowered. Nevertheless, the above studies suggest that the anxiolytic, antipsychotic and neuroprotective effects of CBD may improve the psychological, cognitive and brain health commonly related to long-term cannabis use [24]. This may be an added benefit of using high-dose CBD in people seeking treatment for CUD and identifies potential ‘secondary outcomes’ for future studies.

### What are suitable primary endpoints for clinical trials of CUD treatment?

A challenge in embarking on clinical trials for substance use disorder is choosing a primary endpoint. Whilst historically abstinence (cessation of all use) has often been used in cannabis treatment research, there is increasing recognition that abstinence may not be the primary goal of treatment for patients who use cannabis. A recent consensus expert panel identified suitable outcomes when undertaking clinical trials for the treatment of CUD [50], recommending primary outcomes of (a) self-reported frequency of use, using the Time Line Follow Back (TLFB) method [51]; (b) biological assessment of cannabis use, with urinalysis of the metabolite THC-COOH or oral fluid detection of THC; and (c) severity of CUD, using a structured instrument measuring DSM-5 Criteria (e.g. Mini-International Neuropsychiatric Interview (MINI) [52]). In line with these recommendations, and consistent with the previous Phase 2a RCT, we propose to use two primary endpoints to measure illicit cannabis use: (1) self-reported ‘cannabis-free days’ and (2) urinary THC-COOH, across the 12-week treatment period of the study, alongside a range of secondary outcome measures.

### Cannabis use in Indigenous Australian populations

Cannabis use is more prevalent among Aboriginal and Torres Strait Island people than non-Indigenous Australians. Data from the 2019 National Aboriginal and Torres Strait Islander Health Survey [53] indicated 24% (31% males, 18% females) of Indigenous people aged ≥ 15 years reported cannabis use in the past year, an increase from 19% in the corresponding 2012–2013 survey, and 30% higher than non-Indigenous Australians [53]. The elevated prevalence of illicit drug use among Indigenous Australians could be attributed to personal and familial factors, including intergenerational trauma from colonisation and experiences of racism. Societal-level influences such as persistent social and economic marginalisation contribute significantly to the increased likelihood of substance use amongst Indigenous Australians [1, 2].

Not only are prevalence rates of CUD higher, but the harms also resulting from cannabis use are greater in Indigenous Australian communities. Indigenous Australians are five times more likely to be hospitalised for CUD than non-Indigenous Australians [54] and six times more likely to seek treatment for cannabis use than non-Indigenous Australians when adjusted for age [2].

Yet despite the high prevalence of cannabis use and related harms in Indigenous Australians, to date, there have been no clinical treatment trials for CUD among Indigenous Australian populations. This study aims to ensure that a representative proportion of Indigenous Australian participants, with a target of 20% of the total sample, are recruited to the study. The target reflects the proportion of Indigenous Australian clients attending for cannabis treatment in participating study sites, with representation of Aboriginal researchers, health workers and consumers at all levels of the project governance (see Methods).

### Summary

Cannabis Use Disorder poses significant health and social risks. Existing psychosocial treatments for CUD have modest effects, prompting the exploration of effective medications. CBD has emerged as a promising treatment for CUD, backed by preclinical evidence, and pilot data from a recent Phase 2a RCT. CBD offers additional advantages by potentially alleviating the mental health, and cognitive impairments associated with prolonged cannabis use.

## Methods

### Research hypothesis and study aims

The *research hypothesis* is that CBD, compared to placebo, will achieve statistically and clinically significant reductions in cannabis use, as measured by the number of self-reported cannabis-free days and urinary THC-COOH levels, among treatment-seeking patients with moderate-severe CUD.

The *primary aim* of the CBD-CUD study is to examine the efficacy of CBD, compared to placebo, in reducing cannabis use (as measured by self-report and quantitative measures of cannabis metabolites (THC-COOH) in urine drug screens) during treatment (Weeks 1–12) in participants seeking treatment for moderate-severe CUD, when used in combination with psychological interventions.

*Secondary aims* include examination of (i) safety, (ii) other cannabis related measures (e.g., cannabis withdrawal and cravings, cannabis-related problems); (iii) tobacco and other substance use; (iv) health and quality of life (QoL) measures, (v) patient experience measures; (vi) treatment retention rates; (vii) cognitive performance; (viii) post-treatment (Week 24) cannabis use, health outcomes and QoL measures.

### Study design

The study is a parallel group prospective double-blind Phase 3 randomised controlled trial comparing a 12-week treatment period of oral CBD (400 mg daily) (Experimental) to placebo (Control), with both groups receiving 4 sessions of manualised CBT-based counselling. Research interviews will be conducted at baseline (week 1), 3-weekly during the study intervention (weeks 4, 7, 10 and 13) and 12-weeks after the end of treatment (week 25) (Fig. 1). The study will use a modified intention-to-treat analysis. The expected number of participants is 250, of which we estimate approximately 20% (*n* = 50) will be of Indigenous background. The study will also include qualitative interviews with Indigenous Australian participants in both control and intervention groups (a total of *n* = 15–25 Indigenous Australian participants) to examine their experiences in the study.

**Fig. 1 Fig1:**
[figure not shown]
Overview of study design

### Ethical statement

The study will be conducted in accordance with the *National Statement on Ethical Conduct in Human Research* (2007), the *CPMP/ICH Note for Guidance on Good Clinical Practice* and consistent with the principles that have their origin in the Declaration of Helsinki. The study was approved by the Sydney Local Health District Human Research Ethics Committee (no 2022/ETH02467) and the Aboriginal Health and Medical Research Council’s Human Research Ethics Committee (no 2110/23). The project has an Aboriginal Reference Group that oversees all aspects of the study, including data collection and analysis as they relate to Indigenous Australians. The study has been registered on the Australian and New Zealand Clinical Trial Registry (ACTRN12623000526673).

### Setting and study sites

The multicenter trial will be coordinated from the Specialty of Addiction Medicine, Faculty of Medicine and Health, University of Sydney (study sponsor). Treatment will be provided at seven specialist addiction outpatient treatment centers: four in Sydney, one in Newcastle and two in Melbourne, Australia.

### Participants and recruitment

#### Eligibility criteria

The target study population is treatment-seeking adults with moderate to severe CUD under conditions of informed consent. Eligibility will be assessed by an Addiction Medicine or Psychiatry credentialed Study Medical Officer (SMO).

Inclusion criteria*:*Aged 18 to 65 years.Meeting DSM-5 criteria for moderate or severe CUD (≥ 4/11 criteria) [2], with recent frequent cannabis use (≥ 4 days per week in the preceding 4 weeks).Willing and able to provide informed consent to study procedures.Proficient in English at a conversational level sufficient to participate in a counselling intervention.

*Exclusion criteria* aim to exclude individuals with conditions that jeopardise safety or confound data interpretation:Prescribed medicinal cannabis products (e.g., CBD, THC) for any indication in the previous 4 weeks.Another active (past year) moderate-severe substance use disorder other than tobacco; determined on clinical assessment using DSM-5 criteria.Active or severe medical (e.g., pain, epilepsy, cardiovascular disease) or psychiatric (e.g., psychosis, severe affective disorder) conditions based on clinical assessment.Moderate to severe hepatic disease (transaminase elevations > 3 times, bilirubin > 2 times upper normal limits at screening).Pregnant or lactating women (based on urine β-hCG at screening).Hypersensitivity to CBD or any excipients of Investigational Product.Using medications with known drug-drug hepatic CYP-450 interactions with CBD: 3A4, (e.g., carbamazepine, fluvoxamine, methadone), 2C19 (e.g., rifampin); CYP2B6 (e.g., bupropion), CYP2C9 (e.g., warfarin).Not available during treatment or follow-up (e.g., travel, impending residential detoxification or residential rehabilitation admission, impending imprisonment).Court-mandated treatment requiring abstinence from drugs.Current active (counselling and/or medication-based) treatment for CUD.Received an investigational medicinal product within the last 4 weeks (or 5 half-lives if using long-acting investigational drugs).

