#### Participant numbers

Sample size calculations are based on the analysis of the primary outcome, that is, the difference between placebo and CBD groups in total number of Cannabis-free Days over the 12-week intervention period. Ferguson has suggested that the minimum effect size (Cohen’s *d*) for an effect of practical clinical significance is 0.4167 [55]. To achieve 90% power (two-tailed) and α = 0.05, a total of *N* = 250 (*n* = 125 per group) participants are needed to detect a between-group effect size of *d* = 0.41. Of the target 250 sample, it is estimated approximately 20% (*n* = 50) of the study sample (*N* = 250) will be Indigenous Australians.

Participants who discontinue study procedures after commencing study interventions (medication dispensed on Day 1) will not be replaced in the study but will be included in the modified intention-to-treat analyses. Participants enrolled and randomised, but do not commence any treatment (no medication dispensed or other clinical interventions) will not be included in the final analysis.

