	Marijuana Craving Questionnaire – short form (MCQ) [66]	12 items on a 7-point Likert scale, with 1 = strongly disagree to 7 = strongly agree. The MCQ is a self-report instrument that assesses marijuana craving along 4 dimensions; compulsivity, emotionality, expectancy and purposefulness. Continuous (average item score as a 0–10 range, converted to a z-score)	Research Interview: Week 1 (baseline), 4, 7, 10, 13 and 25
	Marijuana Problems Scale (MPS) [67, 68]	19-item MPS measuring potential negative effects of marijuana on social relationships, self-esteem, motivation and productivity, work and finances, physical health, memory impairment and legal problems on a 3-point Likert scale, with 0 = no problem, 1 = minor problem or 2 = serious problem. Continuous (total count of problems (0–19) or as a summed total of severity rating (0–38)	Research Interview: Week 1 (baseline), 13 and 25
	Urine Drug Screen	Urinary Drug Screen (UDS) collected to analyse for quantitative creatinine adjusted THC-COOH and CBD-COOH. Continuous (ng/ MoL)	Research Interview: Week 1 (baseline), 4, 7, 10, 13 and 25
**Other Substance Use**	Australian Treatment Outcomes Profile (ATOP) [69]	3-Part Questionnaire: 1. Substance use; items refer to substance use over the last 4-weeks, in particular: alcohol, amphetamines, benzodiazepines, heroin, other opioids, cocaine, other substances and tobacco 2. Injecting risk behaviour; 2-items exploring injecting behaviour in the last 4-weeks 3. Health and Well-being; 11-items investigating the participants’ accommodation arrangements, psychological and physical health and quality of life Bounded count (days of use/ abstinence in previous 28-days)	Research Interview: Week 1 (baseline), 4, 7, 10, 13 and 25
	Fagerstom Test for Nicotine Dependence (FTND) [70]	6-item questionnaire that measures nicotine dependency, with a total available score of 10. Continuous (range 0–10, converted to z-score)	Research Interview: Week 1 (baseline), 4, 7, 10, 13 and 25
**Mental and Physical Health**	Psychotomimetic States Inventory (PSIa) [71]	48-item questionnaire with subscales in delusional thinking, perceptual distortions cognitive disorganisation, anhedonia, mania, and paranoia. Continuous (range 0–48, total and subscale scores each converted to z-scores)	Research Interview: Week 1 (baseline), 7, 13, and 25

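### The cannabinoid exclusion covers prescribed products only, so current users of non-prescribed CBD are not clearly kept out, which may weaken the CBD-versus-placebo contrast by an unknown amount

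*Protocol article*

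**What the plan says.** The Eligibility criteria section of the protocol article introduces its exclusions as ones that "aim to exclude individuals with conditions that jeopardise safety or confound data interpretation". The first is "Prescribed medicinal cannabis products (e.g., CBD, THC) for any indication in the previous 4 weeks". Two others come near the same ground: "Current active (counselling and/or medication-based) treatment for CUD" and "Using medications with known drug-drug hepatic CYP-450 interactions with CBD". None mentions CBD obtained without a prescription.

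The background section on cannabidiol and CUD describes an anonymous online survey of French residents who had used CBD in the past month: "Respondents reported using CBD primarily to reduce their use of (illicit) cannabis". In the same section, the account of the Phase 2a trial states: "The 200 mg dose arm was eliminated as it was not efficacious following interim analyses".

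On measurement, Table 1 lists "Urinary Drug Screen (UDS) collected to analyse for quantitative creatinine adjusted THC-COOH and CBD-COOH" at weeks 1, 4, 7, 10, 13 and 25. Table 2 has concomitant medications reviewed at weeks 4, 7, 10 and 13. The Data analysis section adjusts the primary model for cannabis-free days in the 28 days before baseline, counselling sessions and nicotine replacement. It lists no term for CBD use outside the trial.

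**The concern.** The first exclusion names CBD and applies whatever the reason for taking it, so what it guards against is exposure to the substance. CBD bought without a prescription is the same exposure, yet the word limiting the criterion to prescribed products leaves it out. This is the scope of a stated rule, not detail left to a longer document. A site that follows the list literally could enrol a current CBD user.

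In the placebo arm such a participant might go on taking the substance under test. In the CBD arm the trial product would be added to CBD already being taken. Either way the difference in exposure between arms is smaller than the design intends. What is at stake is the size of the observable effect and hence the power, on a trial sized with little to spare.

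**Working it through.** **1. The criteria side by side.** Consider three people taking non-prescribed CBD daily.
- One takes it to reduce cannabis. The bar on current medication-based treatment for CUD may catch this person, but it does not say whether self-sourced CBD counts as treatment, so sites could differ.
- One takes it for sleep or anxiety. That bar does not apply, because the CBD is not treatment for CUD.
- One takes it with no interacting drug. The CYP-450 item concerns drugs that interact with CBD, not CBD itself.

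The gap is therefore real but partly covered.

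**2. The plan's own sample size.** Inputs from Participant numbers: "To achieve 90% power (two-tailed) and α = 0.05", d = 0.41, 125 per group. By the normal approximation,

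n per arm = 2 × (1.96 + 1.2816)² / 0.41² = 21.02 / 0.1681 = 125.01, rounded up to 126 (252 in total).

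Power at 125 per arm = Φ(0.41 × √(125/2) − 1.96) = Φ(3.241 − 1.960) = Φ(1.281) = 0.900. The t-test version gives 0.898. The stated 250 reproduces.

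**3. Attenuation under assumptions.** Let f be the share of the placebo arm taking non-trial CBD throughout treatment, and e the fraction of the trial product's effect that it gives them. Assume that extra CBD changes nothing in the CBD arm and that the SD is unchanged. Then

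d* = 0.41 × (1 − f × e), and power = Φ(d* × √(125/2) − 1.96).

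Worked case, f = 10% and e = 1: d* = 0.41 × 0.90 = 0.369; 0.369 × 7.906 = 2.917; Φ(0.957) = 0.831.

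| f | e = 0 | e = 0.5: d*, power (total N for 90%) | e = 1: d*, power (total N for 90%) |
|---|---|---|---|
| 5% | 0.900 | 0.400, 0.885 (264) | 0.390, 0.869 (278) |
| 10% | 0.900 | 0.390, 0.869 (278) | 0.369, 0.831 (310) |
| 20% | 0.900 | 0.369, 0.831 (310) | 0.328, 0.737 (392) |

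Both f and e are assumptions; the article gives neither. The figures are on the scale of the plan's own sample-size calculation for cannabis-free days. The article gives no sample-size calculation for THC-COOH, so none is offered here.

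**The case against.** Several points on the other side stand.

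- **Prevalence is unknown.** The survey recruited people who already used CBD, in France, and the article itself notes its sampling bias. It shows that the behaviour exists. It does not show how common it is among Australian treatment-seekers.
- **A full effect is unlikely.** It would require self-obtained CBD to work as well as the trial regimen. The article reports the 200 mg arm as not efficacious, though that arm had 12 people over four weeks. Entrants must also have used cannabis on at least 4 days a week over the preceding 4 weeks, so anyone enrolled while on CBD is still a frequent user. The e = 1 column is an upper bound on the loss.
- **Baseline adjustment helps somewhat.** Adjusting for prior cannabis-free days absorbs part of any effect already present at entry. It does not restore a CBD-versus-no-CBD difference among people taking CBD in both arms.
- **Detection is largely available.** Concomitant medications and CBD-COOH are both collected, although the article ties neither to eligibility nor to the primary model.
- **The article is condensed.** Rules on products taken during treatment may well be in the full protocol, and their absence here is no fault.

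It can also be argued that adding the trial product to whatever people already take is a legitimate comparison. That would be easier to accept if the list did not already exclude prescribed CBD taken for any reason.

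A reader might infer that nothing in the list stops a self-treating CBD user. That goes too far, because the bar on current CUD treatment may stop some.

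**Conclusion.** The point holds as a gap in the wording of a stated criterion. Non-prescribed CBD is not clearly excluded, which is hard to square with the purpose given for the exclusions. The consequence is conditional: it needs a non-trivial share of such users, continued use during treatment, and a dose that has some effect. For shares of 5% to 20%, power at 125 per arm runs from 90% (no effect) through 88.5% to 83% (half effect) to 87% to 74% (full effect).

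Three stronger readings are tempting and are not supported:
- **That the primary contrast is in fact diluted, or the sample size wrong.** The article gives no prevalence or dose, and its 250 reproduces.
- **That the result would be biased in favour of CBD.** Randomisation should balance such users across arms, so the expected direction is towards no difference.
- **That wider wording would make baseline free of CBD, or baseline CBD-COOH easy to read.** The article describes CBD as a constituent of the cannabis plant, and every entrant is a frequent cannabis user.

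**What to change.** Reconcile the criterion with its stated aim by extending the existing 4-week exclusion to CBD products whether prescribed or not. State that illicit cannabis itself stays outside it. The same wording would settle whether self-sourced CBD is covered, without relying on how a site reads the bar on current CUD treatment.

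Ask about non-prescribed CBD in the structured history already taken at medical screening, and identify non-trial CBD use through the concomitant-medication reviews already scheduled. Rules on what participants may take during treatment are a matter for the full protocol.

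The cost is a short eligibility amendment and one question at contacts already held. The downside is that a few otherwise eligible people are delayed or excluded. No change to the sample size follows from this point.
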